**Appendix 5: Cockcroft Gault Equation**

$$CL_{cr} = \frac{(140 - age) \bullet ABW}{72 \bullet S_{cr}} \quad (\text{multiply by 0.85 for females})$$

where : CLcr – estimated creatinine clearance

Age – in years

ABW – actual body weight at screening (kg)

Scr – serum creatinine at screening (mg/dL)

from: Cockcroft DW, Gault MH. Prediction of creatinine clearance from serum creatinine. *Nephron*. 1976; 16:31-41.

## **Appendix 6: Method for Lumbar Puncture and intrathecal drainage, adverse event management and CSF Collection**

### **Protocol specific Lumbar Puncture method and sample collection**

The following methodology describes the procedure for introduction of a lumbar intrathecal catheter for continuous and prolonged external lumbar drainage, for the purpose of assessing CSF outflow resistance and diagnostic assessment for confirmation of suitability for a ventriculoperitoneal shunt. This approximates to that which will be used in this study, but the actual clinical application may vary in detail according to local practice.

Subjects will be placed in the lateral decubitus position and, after application of intradermal lidocaine anaesthesia, a [17-g]\* Touhy spinal needle will be inserted through the L3/4, L4/5 or L5/S1 interspace. After entry into the subarachnoid space, a [19-g]\* polyamide catheter will be advanced rostrally 10–15 cm, and secured externally with adhesive tape. The subarachnoid catheter will be extended with [0.8 mm]\* ID silicon tubing which will be attached to a peristaltic pump (Moeller, Neurosurgery, LiquoGuard). The total dead space in this system will be about 1.2 mL. Approximately 1 h after subarachnoid catheter placement, CSF sampling will be initiated. CSF will be withdrawn at a rate of 0.05 mL/min, and collected in 3mL fractions (i.e. 3 mL/hr). The samples will then be frozen on dry ice at bedside within 30 min of collection. The total volume of CSF withdrawn will be about 25–33 % (3mL/hour) of the normal daily CSF volume produced. The catheter will be withdrawn approximately 30 hours after placement.

\* Precise dimensions for needles and tubes will be determined by the Investigator according to local practice and details of equipment not specified will be provided after acquisition.

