### 1.3. Benefit Risk Assessment and Risk Management

#### 1.3.1. Summary of Benefit Risk Assessment

Safety profiles of anti-beta-amyloid antibodies vary significantly (see Section 1.1.2). Hence findings like vasogenic oedema found specifically under treatment with bapineuzumab appear not to be class effects. GSK933776 differentiates from other anti Aβ antibodies as amino acid substitutions in the Fc region of GSK933776 have been introduced to substantially reduce complement activation and Fc receptor binding, thereby decreasing the possibility of inducing immune-mediated tissue damage in case the antibody bound directly to cerebral Aβ. In any case, direct binding to cerebral amyloid appears to be very unlikely based on our observation that we have not detected any brain penetration and the mode of action being based on peripheral binding of Aβ (see Section 1.1.3).

GSK933776 has exhibited a favourable safety profile in the first time in human study BA1106006 to date, in particular no cases of vasogenic edema or microbleeds have been detected on MRI in patients who received GSK933776, or antibodies to GSK933776. Before doses are administered in this study, they will have been assessed in the study BA1106006 as having a favourable benefit risk ratio. This will be based on 8 weeks of safety data and 3 weeks of PK and PD data. All dose escalation decisions in BA1106006 are confirmed by an independent data monitoring committee.

It is planned to collect hourly CSF samples over a period of 22 hours. A CSF catheter will be placed and continuously drained CSF will be collected by a pump at a rate of 3 ml/hour. This is in line with the estimated rate of CSF production in AD patients of 0.2 ml/min (12 ml/hour) and a total CSF volume in human is approximately 250 - 270 ml.

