4. CSF and blood samples will be continuously collected every hour over a period of 22 hours, these include approximately 9 hours for baseline and 12 hours for post dose. After three and six subjects are completed, the results will be reviewed and the sample collection times for both baseline and post dose may be adjusted according to the data from these subjects.
5. This test is for the subject with women with childbearing potential only.
6. ECG and vital sign at 22 hour should be performed before patient leave the Clinical Unit
7. Follow-up day 7±1 day and follow-up day 56 ± 3 days

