## **7. STUDY ASSESSMENTS AND PROCEDURES**

This section lists the parameters of each planned study assessment. The exact timing of each assessment is listed in the Time and Events Table (Section 4.6). Detailed procedures for obtaining each assessment are provided in the Study Procedures Manual (SPM). Whenever vital signs, 12-lead ECGs and blood draws are scheduled for the same nominal time, the assessments should occur in the following order: 12-lead ECG, vital signs, blood draws. The timing of the assessments should allow the blood draw to occur at the exact nominal time.

The timing and number of planned study assessments, including safety, pharmacokinetic, pharmacodynamic, biomarker assessments may be altered during the course of the study based on newly available data (e.g. to obtain data closer to the time of peak plasma concentrations) to ensure appropriate monitoring. The change in timing or addition of time points for any planned study assessments must be approved and documented by GSK, but this will not constitute a protocol amendment. The IRB/IEC will be informed of any safety issues that require alteration of the safety monitoring scheme. No more than 200 mL of blood will be collected over the duration of the study, including any extra assessments that may be required.

It is expected that approximately 66 mL (collecting 3mL CSF per hour) will be collected for 22 hour continuous lumbar puncture per subject during the study.

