## **7.7. Lumbar puncture, insertion of CSF catheter and continuous CSF drainage**

The lumbar puncture and insertion of CSF catheter will be carried according to local hospital procedures by a qualified and experienced medical person or surgeon. For details of the procedures refer to [Appendix 6](#) and SPM.

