### **Insertion of CSF catheter and continuous CSF drainage**

Continuous CSF sampling will be performed i) to better understand the pharmacodynamics of GSK933776, ii) to assess for quantifiable levels of GSK933776 and iii) to provide safety information on potential adverse events. CSF samples will be continually obtained from all enrolled subjects for **22** hours and 3 mL CSF sample will be collected at each hour (as described in the Time-Events Table, Section [4.6](#)). The continuous CSF collection will be performed according to the standard operating procedures of the study centre, by a physician expert in this procedure, and considering the recommendations outlined in the articles cited in the next paragraph in an effort to

limit the frequency and severity of PLPHA. Subjects will remain supine for 1 hour following the procedure.

There is limited literature on the risk of adverse events specific for use of CSF catheters for continuous drainage, Walchenbach *et al* [Walchenbach, 2002] reported bacterial meningitis in 2 of 38 patients – both recovered after antibiotic therapy - and drain replacement in 5 of 38 patients. Other adverse events that have been described and assumed reason:

- Root irritation (radicular pain, back or leg pain/paresthesia) – catheter proximity to nerve root
- Pneumocephalus – introduction of air into subarachnoid space
- Infection (meningitis) – bacterial contamination of drainage line
- Subdural haematoma and secondary intracranial haematoma – attributable to CSF over-drainage or sudden reduction in CSF pressure, and associated with severe headache

In a study of 15 normal pressure hydrocephalus patients by Chen *et al* [Chen, 1994] no complications due to the drainage procedure were noted.

Bateman RJ *et al.* reported in a population of 20 healthy volunteers undergoing frequent CSF samplings for assessment of the effect of an amyloid beta modulating agent on CSF amyloid beta levels:

- Four postlumbar puncture headaches
- one episode each of dizziness and numbness requiring follow-up magnetic resonance imaging
- increased blood pressure, back and leg pain, and nausea and vomiting in an unspecified number of cases

All adverse events resolved and were considered by Bateman RJ *et al.* as likely being related to lumbar CSF sampling. Nevertheless, as drug administration was part of the study relationship with the study medication cannot be excluded.

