## CSF Amyloid Beta Levels Over Time for Patients 101-103

[figure not shown]

Note: As the CSF sample collecting time point is delayed for approximately 1.5 h compare to the real time. Therefore, the actual infusion time is showing as pink column from 9.5 to 10.5 h in this table.

- Removal of the RBANS assessment at the screening

The cognitive instrument RBANS was used in AD patients in an independent GSK study in which ADAS-cog was also used. RBANS did not demonstrate the effect on AD patient as the expectations and hence is now unlikely to be used in further development of the antibody GSK933776.

- Inclusion of patients with dietary controlled type diabetes mellitus

To date no novel microbleeds have been detected in patients who received GSK933776. Dietary controlled type 2 diabetes is common in the AD patient population and the incremental risk of cerebro-vascular disease due to dietary controlled type 2 diabetes is considered to be small. Type 2 diabetes requiring drug treatment will continue to be an exclusion criterion.

- To include an MRI on visit day 56 as additional safety measure

An additional MRI is introduced at 56 day follow up to complement the CNS safety monitoring in place.

- In addition, some minor changes were made for clarification purposes or consistency throughout the protocol

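### Appendix 6 keeps the intrathecal catheter in until about 30 h after placement, although the 22-hour CSF collection is complete at about 23 to 24.5 h

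*Protocol*

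**What the plan says.** Appendix 6, in its subsection on the protocol-specific lumbar puncture method, gives a start and an end for the catheter. The start of sampling: "Approximately 1 h after subarachnoid catheter placement, CSF sampling will be initiated". The removal: "The catheter will be withdrawn approximately 30 hours after placement".

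The rest of the current protocol sets the length of collection at 22 hours:

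- Section 1.3.1: "It is planned to collect hourly CSF samples over a period of 22 hours".
- Section 4.6, footnote 4: "CSF and blood samples will be continuously collected every hour over a period of 22 hours".
- Section 7 expects about 66 mL at 3 mL per hour, which "will be collected for 22 hour continuous lumbar puncture per subject during the study".
- Sections 4.2 and 7.7 also state 22 hours. Section 6.3.1 adds that the total collection time stays the same even if sampling times move relative to the dose.

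Section 7.7 directs sites to the appendix: "For details of the procedures refer to" Appendix 6 and the Study Procedures Manual. No other section gives a removal time. The Time and Events Table, as it can be read here, has a row for catheter insertion and none for removal.

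**The concern.** Both statements are current text and they do not fit together. If collection lasts 22 h and starts about 1 h after placement, nothing remains to be sampled from about 23 h onwards, yet the catheter stays until about 30 h. The appendix gives no reason for the remaining hours.

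What is at stake is subject safety. Section 7.7 lists meningitis as a risk of continuous drainage, attributed to "bacterial contamination of drainage line", and cites a lumbar drainage series with bacterial meningitis in 2 of 38 patients. It also links over-drainage to subdural haematoma. Appendix 6 does not say that the pump stops when the last sample is taken. Hours of dwell that serve no measurement are avoidable exposure, and Amendment 1 shortened the collection partly to lessen the burden on patients.

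**Working it through.** **Inputs**

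- Placement to start of sampling: about 1 h (Appendix 6).
- Collection length: 22 h (Sections 1.3.1, 4.2, 4.6, 7, 7.7).
- Withdrawal rate: 0.05 mL/min = 3 mL/h; dead space 1.2 mL (Appendix 6).
- Lag of the sample clock, from the figure note for the first three patients in Appendix 7: "As the CSF sample collecting time point is delayed for approximately 1.5 h compare to the real time".
- Catheter removal: about 30 h after placement (Appendix 6).
- CSF production: 12 mL/h (Section 1.3.1).

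**Check of the volume.** 3 mL/h × 22 h = 66 mL. Section 7 is correct.

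**End of collection and idle dwell.** End = start lag + 22 h + any further delay; idle dwell = 30 h − end.

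| Reading of the clock | End of collection (h after placement) | Idle dwell (h) |
|---|---|---|
| 22 h counted from placement | 22 | 8.0 |
| 1 h start lag | 1 + 22 = 23 | 7.0 |
| 1 h lag + dead space (1.2/3 = 0.4 h) | 23.4 | 6.6 |
| 1.5 h lag taken to include the start lag | 22 + 1.5 = 23.5 | 6.5 |
| 1 h lag and 1.5 h lag both added | 24.5 | 5.5 |

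The last row probably counts the start lag twice, since 1 h + 0.4 h is already close to 1.5 h. It is kept as the reading most favourable to the plan apart from local variation. The best single estimate is about 6.5 h.

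Relative size:

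- Against the time needed: 7/23 = 30% longer; 5.5/24.5 = 22% longer.
- As a share of the 30 h dwell: 7/30 = 23%; 5.5/30 = 18%.

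**Where the 30 h fits.** With the superseded 30-hour collection, sampling would end at 30 h (clock from placement) or 31 h (1 + 30). The sentence matches that schedule. Amendment 1 changed the collection from 30 to 22 h; neither its list of changes nor that of Amendment 2 includes Appendix 6.

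**A second figure in the same paragraph.** Appendix 6 puts the CSF withdrawn at 25 to 33% of daily production. Taking 12 mL/h × 24 h = 288 mL per day, 66/288 = 23% and 90/288 = 31%. The old volume falls in the range and the current one does not. This points the same way but is not decisive: the figure could be meant as a ratio of rates (3/12 = 25%), which does not depend on duration.

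**If the pump ran until removal.** 3 mL/h × 5.5 to 7 h = 16.5 to 21 mL more CSF, or 16.5/66 = 25% to 21/66 = 32% above the stated 66 mL. The protocol does not say whether it would.

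**The case against.** The best defence is that Appendix 6 does not claim to be the study schedule. It describes a drainage method used to assess suitability for a shunt, calls this an approximation of what the study will do, and lets sites depart from it in detail. Both times are approximate. Section 7.7 also puts the procedure under local hospital procedures, the centre's own operating procedures and the Study Procedures Manual, any of which may fix earlier removal; none is at hand. The 22 h ECG and vital signs (Section 4.6, footnote 6) are placed before the subject leaves the unit, which suggests that sites may tie discharge to the end of sampling. Finally, the extra hours would largely be supervised: observation for 18 to 20 h after dosing (Section 7.2.4) runs to about 27 to 30 h on the sampling clock if the dose is at 9 to 10 h.

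Some of this stands. It is not shown that any site would keep the catheter in to 30 h, and the harm cannot be sized: the 2 of 38 comes from an outside hydrocephalus series, and the protocol does not give its drainage duration.

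It does not remove the inconsistency. The appendix leaves needle and tube dimensions to the investigator, but not dwell time. It is the place to which Section 7.7 sends sites, and its 30 h is the only removal time in the protocol. Observation for allergic reactions keeps the subject on the unit but needs no intrathecal line. A manual with the right time would still conflict with the protocol appendix.

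**Conclusion.** The point holds. As written, Appendix 6 leaves the catheter in about 5.5 to 7 h after the scheduled CSF collection is complete, with about 6.5 h the most likely figure, and states no purpose for that time. This rests on the 1 h start and the 22 h collection as the protocol gives them, and on sites following the appendix where nothing else in the protocol gives a removal time.

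It is a procedural and safety correction, not a statistical one. The likely analysis windows in Section 4.2 (6 to 8 h for baseline, 2 to 5 h after dosing) lie inside the 22 h, and no endpoint, sample or dosing decision changes. It is still worth making, because the exposure is invasive and the correction is simple.

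**What to change.** In Appendix 6, replace the removal sentence with: *Drainage is stopped and the catheter withdrawn once the 22 h sample is complete, about 23 to 24.5 h after placement.* Tying removal to the event means that the sentence stays right whichever lag applies.

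Two optional additions: a catheter-removal entry after the 22 h sample in the Time and Events Table, and, in the same Appendix 6 paragraph, a restated share of daily CSF (66 mL is about 23% of 288 mL) if a share of total volume is meant.

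If there is a clinical reason to keep the catheter until 30 h, state it in Appendix 6 and say whether the pump is stopped meanwhile. The Study Procedures Manual should be checked for the same figure.

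The cost is one sentence and, if wanted, one table entry. No sample or analysis is lost.

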### **Management of Lumbar Puncture associated AEs**

All adverse events related to the lumbar puncture technique and CSF collection will be managed by the Principal Investigator according to his judgment of best clinical practice.

The most common side effect of Lumbar Puncture is headache. If necessary this may be treated with an epidural blood patch which generally relieves the headache but is not normally deemed necessary. The technique for this procedure is described briefly below:

The subject is placed in the lateral position, after which the back is flexed, sterilised and draped. Sterile gloves are used. A needle (e.g. Spinocan canule: 0.9 × 88 mm/206 × 3.5) is placed in the epidural space, using the loss of resistance technique. Subsequently, 20 mL of blood is then drawn from the antecubital vein, and injected slowly into the epidural space, after which the needle is removed. The subject is held in the supine position for a few minutes, after which there are no further restrictions.

**CSF sample collection equipment**

[REDACTED]

[REDACTED]

[REDACTED]

[REDACTED]

Further information on the LiquoGuard pump (the equipment that will be used for the withdrawal of CSF following lumbar puncture) can be found in the information booklet supplied in the SRM. The salient features are:

- 1) Approved for use in human subjects CE mark according to EU-directive 93/42/EWG
- 2) Incorporates 2 in-line pressure transducers, thus removing requirement for connection of lumbar line to separate manometer.
- 3) Minimises CSF spillage and dramatic changes in CSF pressure and reduced potential for infection
- 4) Accurate and controllable withdrawal of defined CSF volumes

## Appendix 7: Protocol Amendment Changes

### AMENDMENT 2

#### Where the Amendment Applies

This amendment will apply to all sites/countries for this study

#### Summary of Amendment Changes with Rationale

In this study, GSK933776, a humanised anti-human A $\beta$  IgG1 monoclonal antibody (mAb), is administered to patients with mild AD or mild cognitive impairment (MCI)/early AD to investigate its pharmacodynamic (PD) effects in cerebrospinal fluid (CSF) and plasma.

The sequential dose escalation design developed at the outset of the clinical study BA1113043 reflected the limited safety information for GSK933776 available at the time. Meanwhile safety data from the first time in human (FTIH) study BA1106006 is available for doses up to 6 mg/kg (repeat dosing every 28 days over 8 weeks i.e. 3 administrations). This dose was well tolerated and resulted in peak-trough-ratios of  $\leq 2$  for total amyloid beta 1-42 and 1-34+ in plasma after the first administration (see ref supplement 01 for version 3 of the investigator brochure for GSK933776). Assessment of the effects of single doses of 6 mg/kg appears to be the fastest route to achieve the objectives of the study with potentially the smallest number of patients. These findings are considered indicative that most of amyloid beta is captured at this dose giving it the best chances to detect the immediate pharmacodynamic effects in CSF. Therefore, the purpose of this protocol amendment is to change the study design of the sequential dose escalation in option 2 and to allow subjects administered with 3mg/kg and 6mg/kg doses in parallel.

#### List of Specific Changes

##### Change 01: Section 1.2.4. Dose Rationale, Table 1 and Paragraph 4

PREVIOUS TEXT

| Dosing   | CSF levels : Free AND Total A $\beta$ 1-42                                     | GSK933776 Dose Groups (Cohorts) Assessed |
|----------|-------------------------------------------------------------------------------------------|------------------------------------------|
| Option 1 | >100 pg/ml mean change from baseline of unbound amyloid beta 1-42               | 0.1 mg/kg and 3 mg/kg                    |
| Option 2 | <math>\leq 100</math> pg/ml mean change from baseline of unbound amyloid beta 1-42 | 3 mg/kg and 6-10 mg/kg                   |

Generally, only doses that have proven to be well-tolerated in the first time in human study BA1106006 will be administered in this study. In BA1106006 safety, PK and PD are assessed after each dose level by GSK internal experts and an independent data monitoring committee. Eight weeks of safety data and plasma A $\beta$  levels over 21 days after administration of 1 mg/kg will be provided before commencing this study. Prior to the administration of GSK933776 at doses of 3 mg/kg and 6-10 mg/kg, 8 weeks safety data and plasma A $\beta$  levels over 21 days at the same dose level will be reviewed

(Figure 4). If it was decided to administer a lower top dose instead of the 10 mg/kg in the first time in human study BA1106006 then this dose would be used in this study (BA1113043) dose group 3.

#### REVISED TEXT

| Dosing   | CSF levels : Free AND Total A $\beta$ 1-42                       | GSK933776 Dose Groups (Cohorts) Assessed |
|----------|-----------------------------------------------------------------------------|------------------------------------------|
| Option 1 | >100 pg/ml mean change from baseline of unbound amyloid beta 1-42 | 0.1 mg/kg and 3 mg/kg                    |
| Option 2 | ≤ 100 pg/ml mean change from baseline of unbound amyloid beta 1-42   | 3 mg/kg and 6-10 mg/kg                   |

Generally, only doses that have proven to be well-tolerated in the first time in human study BA1106006 will be administered in this study. In BA1106006 safety, PK and PD are assessed after each dose level by GSK internal experts and an independent data monitoring committee. Eight weeks of safety data and plasma A $\beta$  levels over 21 days after administration of 1 mg/kg will be provided before commencing this study. Prior to the administration of GSK933776 at doses of 3 mg/kg and 6-10mg/kg, 8 weeks safety data and plasma A $\beta$  levels over 21 days at the same dose level will be reviewed (Figure 4). If it was decided to administer a lower top dose **6mg/kg** instead of the 10 mg/kg in the first time in human study BA1106006 then this dose would be used in this study (BA1113043) **as** dose group 3.

